### Quality assurance

To ensure high-quality execution of the trial in accordance with the protocol, all trial staff will be trained by the chief investigators and provided with a standard protocol book which contains details of standard operating procedures, trial contacts, visits, measurements, monitoring and case report forms. Data are collected using the same forms across sites, these data are checked by staff in Hobart and any discrepancies are clarified.

### Primary outcomes

We have two primary outcomes for this study, assessing improvements in symptoms and structural progression. These are change in knee pain assessed by VAS over 24 weeks and change in effusion-synovitis volume assessed from MRI. All outcomes and time points of assessment are listed in Table 2.

**Table 2 Tab2:** Primary and secondary outcomes

Outcome	Time points
Primary outcomes	
Knee pain: VAS score	24 weeks
Knee effusion-synovitis: maximal area, volume, ordinal measures (MRI)	24 weeks
Secondary outcomes	
BML: maximal area	24 weeks
Effusion volume (ultrasound)^γ^	24 weeks
Knee pain: VAS score	4, 8, 12, 16, 20 weeks
Knee pain: total WOMAC pain, weight bearing and non-weight bearing pain	all time points
Hand and back pain (VAS)	All time points
Knee function	All time points
OMERACT–OARSI responder criteria [41]	All time points
hs-CRP	12 and 24 weeks
Blood lipids	12 and 24 weeks
Blood glucose	12 and 24 weeks
Leg strength	12 and 24 weeks
Analgesic use	All time points
Quality of life (AQoL-6D)	12 and 24 weeks
Pressure pain threshold testing on study knee^¥^	24 weeks
Adverse events	12 and 24 weeks
Medication persistence	12 and 24 weeks
Cost data: hospitalisation, medication use, joint replacement	

^γ^ Perth only

^¥^ Melbourne and Perth ONLY

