## Objective

We are conducting a multi-centre randomised, placebo-controlled double-blind clinical trial. This will compare efficacy of krill oil vs identical placebo to treat knee OA (both pain and structure) in 260 patients with clinical knee OA, significant knee pain and effusion-synovitis on imaging.

We hypothesise that krill oil (2 g daily) will decrease pain (assessed by 100 mm visual analog scale (VAS)) score by 10 mm more than identical placebo over 24 weeks and decrease effusion-synovitis size over 24 weeks (co-primary hypotheses) and improve knee pain over 4, 8, 12, 16, and 20 weeks (secondary hypotheses) in patients with symptomatic knee OA and knee effusion-synovitis, compared with placebo. If krill oil proves effective, it will offer a novel therapeutic approach to reduce knee OA progression.

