### Sample size calculations

Using data from another trial conducted in our centre [52], assuming 10-mm difference between krill oil and placebo on the VAS pain scale (reduction in VAS pain scores in the placebo group by − 15.5 ± 25.5 mm over 12 weeks) and using assumptions of 90% power and 5% probability of type 1 error (alpha = 0.05), we will need 234 participants. Adjusting for 10% loss to follow-up, we need 260 participants (130 in each arm). Based on data on effusion-synovitis volume in our vitamin D RCT for knee OA, there was 13.7 ml (SD = 10.7) in the placebo group and 13.6 ml (8.1) in the active group (in those with effusion-synovitis at enrolment, i.e., 60%) at baseline [61]. With 234 subjects we will have 90% power to detect a difference of 4.5 ml. It is likely we will see at least a reduction of this amount with a treatment that effectively targets inflammation. What level reflects clinical significance is uncertain but this level is approximately 2.5 times the change that could be expected with measurement error. Furthermore, modelled data from our long-term Tasmanian cohort demonstrates that a reduction in effusion-synovitis size by 4.5 ml will decrease the need for joint replacement by 30% over 13 years (unpublished data).

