### Statistical analysis

The primary analyses will be intention-to-treat analyses of primary and secondary outcomes. Per protocol analyses will be performed as the secondary analyses.

Changes in knee pain, knee effusion-synovitis size and any other outcomes which were collected using a linear scale will be analysed using a linear mixed model with treatment, month and their interaction (treatment × month) as covariates, as well as outcome measured at baseline and the baseline interaction with month. Incidence of adverse events will be assessed using log binomial regression. Correlated data within trial centres and the repeated measures will be addressed using trial centre and patient identification as random intercepts. Month will be treated as random effect to allow different treatment effects among patients over time. The sensitivity of models to the structure for the random effects and covariance structures will be assessed using likelihood ratio tests. Change in outcome measures within each group and differences in changes between groups from baseline to follow-up will be calculated using linear combinations of the estimated coefficients. If there are baseline imbalances in covariates between treatment groups, we will consider adjusting for them based on whether we regard the imbalance as clinically significant. Missing data caused by loss to follow-up and non-responses will be addressed by adding variables that have complete data at baseline and can explain missingness to the regression models.

Secondary analysis for missing data will be performed in people with full medication adherence (e.g., > 80% of softgels) and using imputation. Baseline variables with complete data will be used for data imputation assuming missing at random.

Subgroup analyses will be performed to examine which subgroups may respond better to treatment. These will include effusion size, radiographic knee OA, co-pathology present on MRI, pain characteristics, levels of inflammatory markers and serum lipid measures. Statistical significance will be set as a two-sided *P* value < 0.05.

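### Table 2 makes three effusion-synovitis measures primary where the text and the power statement use volume alone, and co-primary is not tied to a success rule

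*Protocol article*

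**What the plan says.** The Primary outcomes text counts the outcomes: "We have two primary outcomes for this study, assessing improvements in symptoms and structural progression". It identifies the structural one as "change in effusion-synovitis volume assessed from MRI" and then refers the reader to Table 2. The Table 2 row under primary outcomes reads "Knee effusion-synovitis: maximal area, volume, ordinal measures (MRI", assessed at 24 weeks.

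The Abstract, the Objective and the Statistical analysis section speak only of effusion-synovitis size, which does not settle which measure is meant. The Objective links the two hypotheses by one word: "decrease effusion-synovitis size over 24 weeks (co-primary hypotheses".

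The Sample size section treats the outcomes one at a time. For pain: "using assumptions of 90% power and 5% probability of type 1 error (alpha = 0.05), we will need 234 participants". It then gives 90% power with the same 234 participants for a 4.5 ml difference in effusion-synovitis volume. Neither maximal area nor an ordinal score has a power statement. The Statistical analysis section closes with "Statistical significance will be set as a two-sided *P* value < 0.05" and gives no split, order or joint rule.

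**The concern.** The text and the table cannot both be right about what is primary. If Table 2 is followed, the structural outcome is three measures of the same thing, each tested at 0.05, and nothing says whether one of them or all must be favourable. A report could lead with whichever measure gave the best result and cite Table 2 in support.

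Separately, co-primary is used in two ways in practice: both outcomes must succeed, or each may support a claim on its own. The error rate and the power of the trial as a whole differ between the two, and the article does not say which applies.

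**Working it through.** **1. The places side by side**

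- Primary outcomes, text: volume.
- Primary outcomes, Table 2: maximal area, volume, ordinal measures.
- Sample size calculations: volume.
- Abstract, Objective, Statistical analysis: size, not further defined.

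The text and the power statement agree on volume. Table 2 is the outlier. Three is also the smallest count it allows, since ordinal measures is plural.

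**2. Reproducing the volume figure**

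Inputs from the Sample size section: difference 4.5 ml, SD 10.7 ml (the larger of the two baseline SDs), 234 participants, so 117 per arm.

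- n per arm = 2 × (1.960 + 1.282)² × 10.7² / 4.5² = 118.8, rounded up to 119, or 238 in total. This is within 2% of 234.
- Power at 117 per arm: 4.5 / (10.7 × √(2/117)) = 3.217; 3.217 − 1.960 = 1.257; power 89.6%.

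The stated 90% is therefore reproduced for volume alone at an unadjusted two-sided 0.05.

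**3. Error of the structural claim if any of the three measures may carry it**

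The quantity is P(at least one |Z| > 1.96) for three null test statistics with a common correlation, found by simulating multivariate normal values (4 million draws). The article's effusion-synovitis section gives 0.77 for volume with score over the whole joint. The 0.77 and 0.90 for the other pairs are assumptions.

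- Correlation 0.77: 10.2%.
- Correlation 0.90: 8.3%.
- Limits: 5% if the measures are perfectly correlated; 1 − 0.95³ = 14.3% if independent.

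This does not go away if both pain and structure are required. If krill oil truly reduces pain but not effusion-synovitis, the structural test is the only safeguard, and it has this error.

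Counting pain as well, with success on any of four tests, the error is 12.6-14.7% for MRI correlations of 0.77-0.90 and pain-MRI correlations of 0-0.3.

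**4. Pain plus volume only: the two meanings of co-primary**

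*Either suffices, each at 0.05.* Familywise error = 1 − 0.95² = 9.75% if independent. By simulation it is 9.5% at correlation 0.3, 9.1% at 0.5 and 7.8% at 0.8.

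*Both required, each at 0.05.* Type I error is at most 5%. Joint power from the stated per-outcome figures = 0.90 × 0.90 = 81% if independent. From the bivariate normal distribution it is 82% at correlation 0.3, 83% at 0.5 and 86% at 0.8.

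The correlation between pain and volume effects is not given, so all values in this step above 0 are assumptions.

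**The case against.** The best defence is that the text and the power statement both say volume, so a careful reader can tell what was meant. On that view Table 2 groups one imaging domain on one row and does not declare three tests. A joint decision rule is commonly left to the analysis plan, which is not shown, and the 0.05 sentence is a general closing line that does not exclude a hierarchy elsewhere. Much of this stands: the likely intention is volume, and the lack of a rule in the article is not proof that none exists. It does not remove the contradiction, because Table 2 is where the article says all outcomes are listed, and a later plan could cite either place.

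Four stronger readings are tempting and are not supported.

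- *That a stated figure is wrong under every reading.* The article states 90% power for each outcome and never a joint power. If co-primary means both must succeed, and volume is the only MRI primary, 5% holds and no stated figure is contradicted by the choice of rule.
- *That joint power is 76%.* That multiplies 89.6% for volume by 85.1% for pain. The 85.1% comes from the stated pain inputs (10 / (25.5 × √(2/117)) = 3.00; 3.00 − 1.96 = 1.04), so the drop from 81% is mainly a separate question about the pain sample size, not about multiplicity. It also assumes independence and no gain from baseline adjustment.
- *That error reaches 18.5%.* That is 1 − 0.95⁴ for four independent tests, while the article itself reports volume and score as correlated at 0.77.
- *That maximal area has no measurement method.* An article may leave this to the full protocol and the operating procedures it refers to.

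**Conclusion.** Wrong as written, on a narrow point. Table 2 contradicts the text and the power statement on the structural primary outcome. If any of the listed measures may carry the claim, its type I error is about 8-10% instead of 5%. That range rests on correlations of 0.77-0.90, of which only 0.77 for volume with score is documented, and that value describes the measures themselves, not their changes or treatment effects.

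The second part is an undefined term. With co-primary left open, the trial has either a familywise error of about 9.5-9.8% (pain-volume correlation 0-0.3, less if higher) or control at 5% with about 81% joint power (independent outcomes, more if correlated). The article should say which.

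**What to change.** - In Table 2, keep only effusion-synovitis volume at week 24 as the MRI primary and move maximal area and ordinal score to secondary. This follows the protocol's own text and power statement.
- Before unblinding, state the success rule in one sentence. Either both pain and volume must succeed, each at two-sided 0.05, with 90% described as power per outcome; or either may support a claim, under a familywise procedure such as a fixed sequence of pain then volume, or Holm.

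The cost is one table edit and one sentence. Recruitment is complete, so the sample size is not in question here.

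- *Both required:* no adjustment of the 0.05 level, but joint power is below 90%.
- *Fixed sequence:* nothing is lost for pain, but volume is tested only if pain succeeds.
- *Holm:* a little less power per outcome. Taking the stated 90%, power at 0.025 is 84.1%. If the other outcome is also truly affected and independent, Holm gives 0.841 + (0.900 − 0.841) × 0.841 = 89%. If the other outcome has no effect, it stays close to 84%.

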### Other outcome measures

#### Pain intensity

Knee pain, back pain and hand pain will be assessed using a 100 mm VAS by asking “on this line, thinking about your study knee/back/most painful hand, where would you rate your pain, using the last 7 days as a time frame” over 4, 8, 12, 16 and 20 (but not 24) weeks.

We will also assess pain using the Western Ontario and McMasters Universities Osteoarthritis Index (WOMAC) [42], also over the preceding 7 days. Five items of the WOMAC pain scale in 100-mm VAS format [43] will be used to assess pain during walking on a flat surface, going up and down stairs, at night while in bed, sitting or lying, and standing upright during the last 7 days. Items will be summed to create a total WOMAC pain score (range 0–500). Incomplete items will be addressed according to the WOMAC user guide [44]. If only one item is missing, the remaining four items will be averaged and then multiplied by five. The WOMAC pain score will be considered invalid if more than one item is missing.

#### Knee function

Knee function will be assessed using WOMAC [42]. Seventeen items of the WOMAC function scale in 100-mm VAS format [43] will be used to assess function during descending stairs, ascending stairs, rising from sitting, standing, bending to floor/picking up an object, walking on flat surface, getting in/out of the car, going shopping, putting on socks/stockings, rising from bed, taking off socks/stockings, lying in bed, getting in/out of the bath, sitting, getting on/off the toilet, heavy domestic duties, and light domestic duties during the last 7 days. Items will be summed to create a total WOMAC function score (range 0–1700). If two or fewer items are missing, the remaining items will be averaged and then multiplied by 17 [44]. The WOMAC function score will be considered invalid if more than two items are missing.

#### Magnetic resonance imaging outcomes

An MRI scan of the “study” knee will be performed (screening, week 24). Knees will be imaged in the sagittal plane on a 1.5 T or 3 T whole-body magnetic resonance unit using a dedicated knee coil. Sequences will include T2-weighted fat saturation three-dimensional (3-D) fast spin echo sequence (effusion-synovitis volume, cartilage defects, BMLs); T1-weighted fat saturation 3-D gradient-recalled acquisition sequence (cartilage volume, cartilage thickness); and T2 mapping (Table 3).

**Table 3 Tab3:** Magnetic resonance imaging sequences and parameters

Study site	Machine and coils	T2 weighted sagittal 3D	T1-weighted sagittal 3D	T2 mapping
Hobart	1.5 T whole-body MR unit (GE Optima 450 W, Milwaukee, USA), using a dedicated Transmit/Receive 8-channel knee coil where patient size permits, if body habitus is too large we use a 16 channel large GEM Flex coil	T2 weighted fat-saturated 3D fast spin echo sequence; repetition time 2300 ms; echo time 80 ms; field of view 18 cm; 256 × 256 matrix with interpolation Recon Voxel 0.35 × 0.35 × 1 mm; 2 excitation; slice thickness 1 mm	T1-weighted fat-saturated 3D gradient-recalled acquisition; flip angle 30 degrees; repetition time 38 ms; echo time 3 ms; field of view 16 cm; 256 × 160 matrix Reconstructed Voxel 0.625 × 1 × 1.5 mm; 1 excitation; slice thickness 1.5 mm	T2 mapping; repetition time 1100 ms; echo time 6.6 ms; field of view 16 cm; 320 × 224 matrix Reconstructed Voxel 0.5 × 0.714 × 3 mm; 1 excitation; slice thickness 3 mm
Perth	1.5 T whole-body MR unit (Siemens, Magnetom Avanto Fit, Erlangen, Germany), using a dedicated Transmit/Receive 15 channel knee coil	T2 weighted fat-saturated 3D fast spin echo sequence; flip angle mode T2; repetition time 1400 ms; echo time 89 ms; field of view 19 cm; 256 × 256 matrix with interpolation Recon Voxel 0.4 × 0.4 × 1.5 mm; 1 excitation; slice thickness 1.5 mm	T1-weighted fat-saturated 3D gradient-recalled acquisition; flip angle 10 degrees; repetition time 13.9 ms; echo time 6.05 ms; field of view 19 cm; 320 × 298 matrix Reconstructed Voxel 0.6 × 0.6 × 1.5 mm; 1 excitation; slice thickness 1.5 mm	T2 mapping (multi echo SE); flip angle 180 degrees; repetition time 1890 ms; echo time 13.8, 27.6, 41.4, 55.2, 69.0 ms; field of view 16 cm; 256 × 256 matrix Reconstructed Voxel 0.63 × 0.63 × 3 mm; 1 excitation; slice thickness 3 mm
Adelaide	3 T whole-body MR unit (Siemens Magnetom Skyra 3Tesla), using a dedicated 15 channel knee coil	T2 weighted fat-saturated 3D SPACE; repetition time 2200 msec; echo time 121 msec; field of view 16 cm; 320 × 320 matrix; 1 excitation; slice thickness 0.6 mm	T1-weighted Water Excitation 3D gradient-recalled acquisition VIBE; flip angle 16 degrees; repetition time 10.4 ms; echo time 5.7 ms; field of view 160 cm; 320 × 298 matrix; 1 excitation; slice thickness 1 mm	T2 mapping (multi echo acquisition); flip angle 180 degrees; repetition time 1750 ms; echo time 13.8/27.6/41.4/55.2/69 ms; field of view 16 cm; 320 × 320 matrix; 1 excitation; slice thickness 3 mm
Melbourne	3 T whole-body MR unit (Siemens, (Skyra 3 T) Magnetom Avanto Fit, Erlangen, Germany), using a dedicated Transmit/Receive 15 channel knee coil	T2 weighted fat-saturated 3D fast spin echo sequence; flip angle mode T2; repetition time 1200 ms; echo time 50 ms; field of view 16 cm; 230 × 320 matrix without interpolation not on; Recon Voxel 0.5 × 0.5 × 0.6 mm; 1 excitation; slice thickness 0.6 mm	T1-weighted fat-saturated 3D gradient-recalled acquisition; flip angle 30 degrees; repetition time 11.7 ms; echo time 5.61 ms; field of view 16 cm; 320 × 320 matrix Reconstructed Voxel 0.5 × 0.5 × 1.5 mm; 1 excitation; slice thickness 1.5 mm	T2 mapping (multi echo SE); flip angle 180 degrees; repetition time 1840 ms; echo time 11.7, 23.4, 35.1, 46.8, 58.5 ms; field of view 16 cm; 307 × 384 matrix Reconstructed Voxel 0.4 × 0.4 × 3 mm; 1 excitation; slice thickness 3 mm
Sydney	3 T whole-body MR unit (Siemens, Magnetom Skyra, Erlangen, Germany), using a dedicated Transmit/Receive 15 channel knee coil	T2 weighted fat-saturated 3D fast spin echo sequence; flip angle mode T2; repetition time 1000 ms; echo time 108 ms; field of view 16 cm; 256 × 256 matrix without interpolation Recon Voxel 0.6 × 0.6 × 0.6 mm; 1 excitation; slice thickness 0.6 mm	T1-weighted fat-saturated 3D gradient-recalled acquisition; flip angle 25 degrees; repetition time 11.6 ms; echo time 4.7 ms; field of view 16 cm; 256 × 256 matrix Reconstructed Voxel 0.6 × 0.6 × 1 mm; 1 excitation; slice thickness 1 mm	T2 mapping (multi echo SE); flip angle 180 degrees; repetition time 2150 ms; echo time 13.8, 27.6, 41.4, 55.2, 69.0 ms; field of view 16 cm; 384 × 326 matrix Reconstructed Voxel 0.42 × 0.42 × 3 mm; 1 excitation; slice thickness 3 mm

##### Knee effusion-synovitis

Effusion-synovitis is defined as the presence of intra-articular fluid-equivalent signal on T2 weighted MRI sequence (Fig. 1). A modified Whole-Organ Magnetic Resonance Imaging Score (WORMS) scoring system will be utilised to assess effusion-synovitis (grade 0 to 3) semi-quantitatively in four regions of interest (ROI; suprapatellar pouch, central portion, posterior femoral recess, subpopliteal recess) in terms of the estimated maximal distention of the synovial cavity. The greatest score for any of the four ROI will be used as maximal effusion of the knee. The intraclass reliability assessed as weighted κ in 50 randomly selected images was 0.63–0.75 in different subregions, and the interclass inter-rater reliability was 0.65–0.79 [45].

**Fig. 1 Fig1:**
[figure not shown]
Example of changes in effusion-synovitis area (cm^2^). Effusion-synovitis size decreased from baseline to follow-up 2.6 years later (**a**, **b**). Effusion/synovitis are present in both the suprapatellar pouch and central portion. Overall, effusion size is smaller at follow-up MRI

Effusion-synovitis volume will be measured using a semi-automated segmentation method according to the intra-articular fluid-equivalent signal on a section-by-section basis in each ROI. The final 3-D volume rendering will be generated using commercial in-house imaging software. Change in effusion-synovitis volume is calculated by subtracting baseline values from follow-up values. The intra-rater reliability was 0.97 in the whole joint (0.98 in suprapatellar pouch and 0.95 in central portion). The inter-rater reliability was 0.99 in the whole joint (0.99 in suprapatellar pouch and 0.93 in central portion). Effusion-synovitis volume was highly correlated with effusion-synovitis score (rho 1/4 0.77, *P* < 0.01 for total; rho 1/4 0.91, *P* < 0.01 for suprapatellar pouch; and rho 1/4 0.77, *P* < 0.01 for central portion) [46].

Differentiating effusions from synovitis on MR images requires administration of a contrast agent (gadolinium), which may cause nephrotoxicity. While this is rare, we do not consider the benefits of such differentiation between synovitis and effusion justifies the risk to our study participants, and hence we have not used it.

##### Bone marrow lesions

Bone marrow lesions (BMLs) will be defined as an ill-defined hyperintensity area in the subchondral bone on MRI. BMLs will be assessed on the sagittal T2 weighted sequences at the medial tibial, medial femoral, lateral tibial, lateral femoral and patella sites using a modified WORMS scoring system [47]. The maximum size of each lesion will also be measured using software cursors applied to the greatest area of the lesion, as previously described [48]. We have demonstrated an intraclass correlation coefficient (ICC) of 0.97 [49] using this method. Total BML size will be calculated as the sum of every lesion within the medial tibial, medial femoral, lateral tibial, lateral femoral and patella sites.

#### Ultrasound

Knees will be imaged using an Esaote Mylab 70 VXG ultrasound machine in Perth (Table 4), with scans undertaken by a single sonographer. Images will be stored to be re-read to determine intra-reader reliability).

**Table 4 Tab4:** Ultrasound parameters

	Suprapatellar pouch	Medial para patella	Lateral para patella
Knee position	30 degrees flexion	Neutral	Neutral
Probe plane	Longitudinal	Transverse	Transverse
Probe position	Probe on the distal thigh, at midline, longitudinal to its major axis	One end of the probe over the patella and the other end over the medial femoral condyle	One end of the probe over the patella and the other end over the lateral femoral condyle
Modes	GS and PD	GS and PD	GS and PD
Settings	To be optimised once machines known	To be optimised once machines known	To be optimised once machines known
Probe sweep	Move lateral to medial side	Proximal to distal side	Move proximal to distal side
Lesions to score	Synovitis (0–3) Synovial hypertrophy (0–1) Effusion (0–1) Effusion depth (mm) Synovial power Doppler signal (0–1)	Synovitis (0–3) Synovial hypertrophy (0–1) Effusion (0–1) Effusion depth (mm) Synovial power Doppler signal (0–1)	Synovitis (0–3) Synovial hypertrophy (0–1) Effusion (0–1) Effusion depth (mm) Synovial power Doppler signal (0–1)
Images to store	Midline longitudinal with the effusion depth measurement in situ	Representative image	Representative image

*GS* grey scale, *PD* power Doppler

Ultrasounds completed in Perth only

Synovitis in the supra patella pouch will be defined as a combination of synovial hypertrophy and effusion (using Outcome Measures in Rheumatology (OMERACT) definitions [50]) and scored on a 0–3 scale with grade 0 = no synovitis, grade 1 = minimal distension of the recess by abnormal internal hypoechoic or anechoic (relative to subdermal fat tissue) material, grade 2 = moderate distension or enlargement of the recess by abnormal internal hypoechoic or anechoic (relative to subdermal fat tissue) material with flat or concave superficial limit, and grade 3 = severe distension or enlargement of the recess by abnormal internal hypoechoic or anechoic (relative to subdermal fat tissue) material with bulging superficial limit. Depth of effusion (mm) will be measured only in the suprapatellar pouch (SPP), from a still midline longitudinal image, measuring the maximal effusion depth in this plane.

In the SPP, medial parapatellar region and lateral parapatellar region, synovial hypertrophy, effusion and power doppler signal (defined using OMERACT definitions [50]) will be scored as absent (0) or present (1).

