## Discussion

We propose a multicentre, randomised, double blind placebo-controlled trial to determine whether krill oil 2 g/day improves knee pain and reduces size of knee effusion-synovitis compared to placebo in people with clinical knee OA, significant knee pain and knee effusion-synovitis. If krill oil proves effective, it will offer a novel therapeutic approach to reduce or slow progression of knee OA.

Krill oil is theorised to have an effect via both anti-inflammatory and anti-oxidative mechanisms. Oxidative stress and inflammation have important roles in OA pathogenesis and krill oil therapy may be beneficial in treating OA. Krill oil (300 mg/day) reduced inflammation (as measured by CRP) by 30% in 30 days vs 25% increase in patients receiving placebo [34]. This may have important clinical implications, with low level inflammation associated with increased loss of tibial cartilage volume (β = − 1.18% per annum per quartile of IL-6) [62]). Accordingly, trials are starting to use MRI-assessed effusion/synovitis as a treatment target. In a trial using low dose oral prednisolone for painful hand OA, MRI-assessed effusion-synovitis was associated with pain cross-sectionally, but not hand pain as assessed by VAS; however, effusions did not change over time with treatment or predict response to treatment [63].

Effusion and synovitis can also be assessed using ultrasound; such effusions predict knee replacements independent of severity of radiographic damage and pain [20]. Presence of ultrasound-detected knee effusions has been used to select people who might respond well to oral methotrexate, which demonstrated efficacy in an open-label trial, albeit without a control group [64]. However, the reproducibility of ultrasound is largely dependent on the operator and ultrasound is not yet well utilised in clinical trials of knee OA. This study will enable comparisons of MRI vs ultrasound indices in assessing change in effusion volume and provide evidence of which imaging modality is of most use in this context.

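### Suprapatellar effusion depth by ultrasound: the stored image carries the first measurement, so re-reading it for intra-reader reliability is likely to overstate that reliability unless an unmarked image is used

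*Protocol article*

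**What the plan says.** The Ultrasound section of the protocol article describes scanning at Perth, "with scans undertaken by a single sonographer", and gives the purpose of image storage: "Images will be stored to be re-read to determine intra-reader reliability".

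Table 4 (Ultrasound parameters) lists what is stored for each region. For the suprapatellar pouch it is "Midline longitudinal with the effusion depth measurement in situ". For the medial and lateral parapatellar regions it is "Representative image", and no measurement is mentioned.

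The text below the table confines the depth measurement to one region: "Depth of effusion (mm) will be measured only in the suprapatellar pouch (SPP), from a still midline longitudinal image". The other ultrasound items are a synovitis grade from 0 to 3 and present/absent scores for hypertrophy, effusion and power Doppler signal.

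Table 2 lists effusion on ultrasound as a secondary outcome at 24 weeks, at Perth only. The Discussion says the trial will allow MRI and ultrasound to be compared in assessing change in effusion, and will "provide evidence of which imaging modality is of most use in this context".

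**The concern.** Intra-reader reliability asks how closely one reader reproduces a measurement without help from the first result. The plan says images are kept for this purpose. For depth, the image it tells the site to keep already shows the answer. A reader who sees where the first measurement was placed, and perhaps its value, is likely to place the second one nearby.

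At stake is the estimate of measurement error for suprapatellar depth, the only continuous ultrasound measure that the text describes. Its error indicates whether a change in depth exceeds reading noise, and it would be a natural input to a comparison of ultrasound with MRI. The Discussion itself notes that ultrasound reproducibility depends largely on the operator, so an honest estimate has value here.

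**Working it through.** **No figure to reproduce.** The article states no ultrasound reliability coefficient, no number of images to be re-read and no target. The check is therefore a comparison of statements, followed by algebra for the direction of any bias.

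**Statements side by side (Ultrasound section and Table 4)**

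| Item | Suprapatellar pouch | Parapatellar regions |
|---|---|---|
| Purpose of storage | re-reading for intra-reader reliability | same |
| Image stored | midline longitudinal, depth measurement shown | representative image, no measurement stated |
| Depth measured, according to the text | yes, on a still midline longitudinal image | no |

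The stored suprapatellar image is of the same type and plane as the one on which depth is first measured. The article mentions no unmarked copy, no hiding of the overlay and no blinding of the re-reader to the first value. Table 4 also lists effusion depth among the items to score in the parapatellar columns. The text restricts depth to the suprapatellar pouch, however, and no mark is described on the parapatellar images, so the check stops at suprapatellar depth.

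**Direction of the bias.** Let T be the depth that a frame truly shows, with variance V between frames. Let e₁ and e₂ be independent reading errors, each with variance s². Let w, between 0 and 1, be the weight the re-reader gives to the visible first measurement. This w is an assumption and has no source in the document.

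- First reading: X₁ = T + e₁
- Second reading: X₂ = w·X₁ + (1 − w)·(T + e₂)
- Difference: X₁ − X₂ = (1 − w)·(e₁ − e₂)
- Variance of the difference: 2(1 − w)²s², against 2s² for independent readings
- Apparent within-reader error variance: (1 − w)²s²
- Covariance of the two readings: V + w·s², against V for independent readings
- Apparent intraclass correlation: (V + w·s²) / (V + s²·(1 − w + w²))

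At w = 0 the last line is V/(V + s²), the true value. At w = 1 it is (V + s²)/(V + s²) = 1. For any w in between, the covariance is higher and the within-reader variance lower than for independent readings, so the apparent reliability exceeds the true one.

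**Size.** The range runs from no bias (w = 0) to apparent perfection (w = 1). Neither w nor V/(V + s²) is in the document, so no point within that range can be preferred.

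**The case against.** The strongest objection is that Table 4 says what to store, not that nothing else is stored. A clean frame may also be kept, the overlay may be removable, and the re-reader may be masked. The Quality assurance section refers to a protocol book of standard operating procedures, which is not shown, and an article may leave the conduct of a re-read to it. Table 4 also looks generic: it leaves the settings open until the machines are known, although the text above it names the machine. This stands as far as certainty goes. It supports *likely to be overstated unless an unmarked image is used*, not *will be overstated*. It does not remove the point, because the article does state both the purpose of storage and the image to be stored, and as written the second works against the first.

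Several stronger inferences are tempting but not supported:

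- *All ultrasound reader reliability is compromised.* The mark concerns depth at one region. It may hint that an effusion was called present in the suprapatellar pouch, but the synovitis grade and the present/absent scores are not described as recorded on the image.
- *The parapatellar images share the fault.* No measurement is stated on them. Whether one chosen frame can represent a sweep is a different question, and the article promises only intra-reader reliability, not scan-rescan reliability.
- *The inflation can be put as a figure.* Any apparent coefficient would only restate the assumed w and the assumed true reliability.
- *The comparison with MRI will be tilted toward ultrasound.* The Discussion does not make intra-reader reliability the criterion, and the Statistical analysis section contains no analysis that uses it.
- *The treatment effect is biased.* The re-read serves reliability only. The described purpose of re-reading gives no reason to think it replaces the original blinded readings in the treatment comparison.

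**Conclusion.** The point holds for suprapatellar effusion depth at Perth. Followed as written, the plan gives a second depth reading made with the first in view, and depth reliability is then likely to be overstated.

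This rests on two assumptions: that the marked frame is the one re-read, and that a reader who sees a mark leans toward it to some degree. If an unmarked frame is used, the problem disappears. The size is unknown and cannot be obtained from the document.

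The consequence is narrow: the depth reliability estimate for one secondary measure at one of five sites, and any weight placed on it when ultrasound is set against MRI. It is worth correcting because the correction is specific and costs little.

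**What to change.** - In Table 4, add an unmarked copy of the same suprapatellar frame to the images to be stored, alongside the marked one.
- In the Ultrasound text, state that the depth re-read uses only unmarked or overlay-removed frames, presented in random order, with the reader blinded to the first value and to the visit.
- Where only marked frames exist, report the depth reliability as an upper bound and say why, including wherever it is cited in a comparison with MRI.

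The cost is one additional stored frame per scan at one site and a sentence or two of text, with no added visit or procedure for participants. The Trial status section gives recruitment as complete in July 2019, and follow-up lasts 24 weeks, so the storage change may reach few or no scans. The re-read rule and the reporting caveat can still be applied to images already held, provided the re-read has not been done. If it has, the caveat alone applies.
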